## STUDY PROTOCOL

[Purpose of the study]

To make clear whether amantadine hydrochloride improves dyskinesias without worsening motor function by a multi-center, randomized, double-blind trial.

[Background of the study]

The prevalence of Parkinson's disease (PD) increases in accordance with aging, and PD is one of the most important brain diseases in Japan. Motor disturbance of PD is caused by mainly degeneration of dopaminergic neurons in the central nervous system, and dopaminergic replacement therapy using L-Dopa or dopamine receptor agonists improves motor symptoms. As a result, an increasing number of patients are treated with dopaminergic replacement therapy for a long time. In a long time therapy there are several issues that include dyskinesias. Dyskinesias are thought to be related to hypersensitivity of the dopaminergic receptors in the striatum and the excessive release of dopamine from the dopaminergic neurons, and in addition, it could be related to stimulation to the N-methyl-D-aspartate (NMDA) type glutamate receptors. Amantadine hydrochloride is approved for treatment against PD. Pharmacological actions of amantadine are dopamine release enhancement, dopamine reuptake inhibition, and in addition, amantadine blocks the NMDA type glutamate receptor. Dopamine release from the striatal dopaminergic neurons is regulated via the NMDA-glutamate receptor, and therefore, amantadine may block dyskinesias. Because the concentrations of dopamine and its metabolites in the brain are not influenced by amantadine in the doses of clinical usage its anti-Parkinsonian effects are thought to be related to its anti-cholinergic action or to blockade of the NMDA-glutamate receptor. In the Treatment Guideline 2002 for Parkinson's disease released from the Japan Neurological Society, the cease of MAO-B inhibitors or de-escalation of L-Dopa are recommended. However the cease of MAO-B inhibitors and L-Dopa de-escalation cause worsening of motor symptoms of PD, and the treatment against dyskinesias without worsening of motor symptoms is preferred. The purpose of the study is to clarify whether or not amantadine improves dyskinesias without worsening of motor function by a multi-center, randomized, double-blind trial.

[Methods]

1. The study design

This is a multi-center, randomized, placebo-controlled, double-blind, cross-over study. A cross-over design is adopted to avoid disadvantage in subjects who are allocated in the placebo treatment because amantadine has beneficial effects against PD.

## 2. Eligibility

Eligible patients are 20 to 75 years-old, diagnosed as PD according to steps 1 and 2 of U.K. Parkinson's disease Society Brain Bank Diagnostic Criteria and presenting dyskinesias of the limbs or the trunk.

## 3. Exclusion criteria

- 1) Patients prescribed with amantadine hydrochloride during the previous 2 weeks
- 2) Patients with psychiatric symptoms such as auditory hallucination or delusions
- 3) According to the following formula, creatinine clearance is less than 75mL/min/1.73m^2

Male :  $(140 - \text{age}) \times \text{weight}(\text{kg}) / (72 \times \text{serum creatinine})(\text{mg/dL})$

Female :  $(140 - \text{age}) \times \text{weight}(\text{kg}) \times 0.85 / (72 \times \text{serum creatinine})(\text{mg/dL})$

- 4) Remarkable liver damage
- 5) Pregnant or possibly pregnant
- 6) History of epilepsy
- 7) Patients who are judged as inappropriate participants in the trial

## 4. Informed consent

Patients who are eligible and not excluded according to the exclusion criteria described above will be informed of the background, purpose, method, spontaneous participation, withdraw rights of the study, and gave written consent. Study subjects can read this protocol if necessary.

## 5. Privacy of study subjects

Data obtained in the study will be handled anonymously.

## 6. Interventions

Patients who meet the criteria and seen between March 2007 and February 2008\*1 were considered for the study.

The Arm 1 intervention consisted of an observation period (2-3 weeks), an administration of amantadine hydrochloride period (27 days), a washout period (15 days), and an administration of placebo period (27 days). The Arm 2 intervention consisted of an observation period, placebo period, a washout period, and an administration of amantadine period. Amantadine was escalated step-by-step (100 mg for 7 days, 200 mg for 7 days and 300 mg for 7 days). Placebo is also administered in a

similar manner. The detailed schedule is shown in the Table 1.

Table 1. Schedule of the study

|          | Visit      | UPDRS
/Rush
dyskinesia
scale | blood sampling | video
recording | Arm 1                      | Arm 2                      |
|----------|------------|---------------------------------------|----------------|--------------------|----------------------------|----------------------------|
| Visit 1  | Day -13    | ○                                     | ○              |                    | Observation period (2-3 W) | Observation period (2-3 W) |
|          | Day -12    |                                       |                |                    |                            |                            |
|          | Day -11    |                                       |                |                    |                            |                            |
|          | Day -10    |                                       |                |                    |                            |                            |
|          | Day -9     |                                       |                |                    |                            |                            |
|          | Day -8     |                                       |                |                    |                            |                            |
|          | Day -7     |                                       |                |                    |                            |                            |
|          | Day -6     |                                       |                |                    |                            |                            |
|          | Day -5     |                                       |                |                    |                            |                            |
|          | Day -4     |                                       |                |                    |                            |                            |
|          | Day -3     |                                       |                |                    |                            |                            |
|          | Day -2     |                                       |                | ○                  |                            |                            |
|          | Day -1     |                                       |                |                    |                            |                            |
| Visit 2  | Day 0 ±3D  | ○                                     | ○              |                    | Active 1.0g /1x1           | Placebo 1.0g /1x1          |
|          | Day 1      |                                       |                |                    |                            |                            |
|          | Day 2      |                                       |                |                    |                            |                            |
|          | Day 3      |                                       |                |                    |                            |                            |
|          | Day 4      |                                       |                |                    |                            |                            |
|          | Day 5      |                                       |                |                    |                            |                            |
|          | Day 6      |                                       |                |                    |                            |                            |
| visit 3  | Day 7 ±3日  | (○)                                   |                |                    |                            |                            |
|          | Day 8      |                                       |                |                    |                            |                            |
|          | Day 9      |                                       |                |                    |                            |                            |
|          | Day 10     |                                       |                |                    |                            |                            |
|          | Day 11     |                                       |                |                    |                            |                            |
|          | Day 12     |                                       |                |                    |                            |                            |
|          | Day 13     |                                       |                |                    |                            |                            |
| Visit 4  | Day 14 ±3日 | (○)                                   |                |                    | Active 2.0g /2xN           | Placebo 2.0g /2xN          |
|          | Day 15     |                                       |                |                    |                            |                            |
|          | Day 16     |                                       |                |                    |                            |                            |
|          | Day 17     |                                       |                |                    |                            |                            |
|          | Day 18     |                                       |                |                    |                            |                            |
|          | Day 19     |                                       |                | ○                  |                            |                            |
|          | Day 20     |                                       |                |                    |                            |                            |
| Visit 5  | Day 21 ±3日 | ○                                     | ○              | ●                  |                            |                            |
|          | Day 22     |                                       |                |                    |                            |                            |
|          | Day 23     |                                       |                |                    |                            |                            |
|          | Day 24     |                                       |                |                    |                            |                            |
|          | Day 25     |                                       |                |                    |                            |                            |
|          | Day 26     |                                       |                |                    |                            |                            |
|          | Day 27     |                                       |                |                    |                            |                            |
|          | Day 28     |                                       |                |                    |                            |                            |
|          | Day 29     |                                       |                |                    |                            |                            |
|          | Day 30     |                                       |                |                    |                            |                            |
|          | Day 31     |                                       |                |                    |                            |                            |
|          | Day 32     |                                       |                |                    |                            |                            |
|          | Day 33     |                                       |                |                    |                            |                            |
|          | Day 34     |                                       |                |                    |                            |                            |
|          | Day 35     |                                       |                |                    |                            |                            |
|          | Day 36     |                                       |                |                    |                            |                            |
|          | Day 37     |                                       |                |                    |                            |                            |
|          | Day 38     |                                       |                |                    |                            |                            |
|          | Day 39     |                                       |                |                    |                            |                            |
|          | Day 40     |                                       |                | ○                  |                            |                            |
|          | Day 41     |                                       |                |                    |                            |                            |
| Visit 6  | Day 42 ±3日 | ○                                     | ○              | ●                  | Washout period (2W)        | Washout period (2W)        |
|          | Day 43     |                                       |                |                    |                            |                            |
|          | Day 44     |                                       |                |                    |                            |                            |
|          | Day 45     |                                       |                |                    |                            |                            |
|          | Day 46     |                                       |                |                    |                            |                            |
|          | Day 47     |                                       |                |                    |                            |                            |
|          | Day 48     |                                       |                |                    |                            |                            |
| Visit 7  | Day 49 ±3日 | (○)                                   |                |                    |                            |                            |
|          | Day 50     |                                       |                |                    |                            |                            |
|          | Day 51     |                                       |                |                    |                            |                            |
|          | Day 52     |                                       |                |                    |                            |                            |
|          | Day 53     |                                       |                |                    |                            |                            |
|          | Day 54     |                                       |                |                    |                            |                            |
|          | Day 55     |                                       |                |                    |                            |                            |
| Visit 8  | Day 56 ±3日 | (○)                                   |                |                    |                            |                            |
|          | Day 57     |                                       |                |                    |                            |                            |
|          | Day 58     |                                       |                |                    |                            |                            |
|          | Day 59     |                                       |                |                    |                            |                            |
|          | Day 60     |                                       |                |                    |                            |                            |
|          | Day 61     |                                       |                | ○                  |                            |                            |
|          | Day 62     |                                       |                |                    |                            |                            |
| Visit 9  | Day 63 ±3日 | ○                                     | ○              | ●                  | Placebo 2.0g /2xN          | Active 2.0g /2xN           |
|          | Day 64     |                                       |                |                    |                            |                            |
|          | Day 65     |                                       |                |                    |                            |                            |
|          | Day 66     |                                       |                |                    |                            |                            |
|          | Day 67     |                                       |                |                    |                            |                            |
|          | Day 68     |                                       |                |                    |                            |                            |
|          | Day 69     |                                       |                |                    |                            |                            |
| Visit 10 | Day 70 ±3日 | ○                                     |                |                    |                            |                            |
|          | Day 71     |                                       |                |                    |                            |                            |
|          | Day 72     |                                       |                |                    |                            |                            |
|          | Day 73     |                                       |                |                    |                            |                            |
|          | Day 74     |                                       |                |                    |                            |                            |
|          | Day 75     |                                       |                |                    |                            |                            |

● plasma concentration of amantadine  
○ CBC, Chemical analysis  
(○) on site investigation or telephone contact

Escalation of trial drugs could be discarded if the patients desired no escalation or adverse effects were detected.

Allocation to Arm 1 or Arm 2 is determined according to a computer-generated randomization plan that includes stratification by severity of dyskinesia (ADL-interfering or not-interfering).

At the end of the observation period and at the day 21 of the amantadine or placebo treatment periods, UPDRS-3, UPDRS-4, video recording of dyskinesias and Rush Dyskinesia Rating Scale\*2 (RDRS), medication, blood sampling, and type of dyskinesias (peak dose, end-of-dose, or biphasic dyskinesia) will be checked. Plasma concentrations of amantadine hydrochloride will be determined at the day 21 of amantadine or placebo periods and at the end of washout period.

#### 7. Target sample size

Target sample size is 60 interventions. The sample size was determined based on the previous study by Snow et al., in which dyskinesia score is expected to be improved by 1.1 (1.6) (mean (SD) points on the UPDRS-IVa by amantadine. It was estimated by power analysis comparing the two means, and calculated as 30 (60 interventions) to achieve a power greater than 80% and an error of 0.05 in the crossover test.

#### 8. Administration of the investigatory product (IP)

Amantadine or placebo will be administered according to the schedule table shown in Table 1.

#### 9. Investigatory product (IP)

Placebo consists of 1.0g of lactate and 0.1g of MgCl2. Active consists of 1.0g of 10% amantadine hydrochloride and 0.1g of MgCl2.

#### 10. Randomization

Randomization is based on a computer-generated plan that was concealed.

#### 11. Limitation and fixation of concomitant medications

For the purpose of the study concomitant Parkinson's disease medications shown in the List 1 will be fixed during the course of the study. Medications in the List 2 will be fixed during the course of the study. Use of amantadine is prohibited. Setting of the deep brain stimulation (DBS) should not be changed during the study period in patients with DBS surgical operation.

List 1. (Concomitant medications for PD)

Levodopa (Dopa, Dopa with carbidopa, Dopa with benzeraside)  
Agonists for the dopamine receptor (bromocriptine, pergolide, cabergoline, talipexole, pramipexole, ropinirol)  
selegiline  
zonisamide  
trihexyphenidyl

List 2 (Anti-psychotic drugs with dopamine receptor inhibition)

tiapride, sulpiride, quetiapine, chlorpromazine, thioridazine, fluphenazine, fludecasin, prochlorperazine, propericiazine, levomepromazine, haloperidol

## 12. Analysis

### Primary outcome measure:

Primary outcome measure is the difference of Rush Dyskinesia Scale from baseline after amantadine hydrochloride and after placebo administration.

The changes of scores from baseline will be compared between amantadine and placebo interventions.

Changes of RDRS will be categorized into improved and not-improved, and data will be analyzed using repeated measure logistic regression incorporating treatment effects (placebo vs active) and period effects (interaction of order effect and carry-over effect).

*P* values of less than 0.05 are considered statistically significant.

Rush Dyskinesia Scale is scored based on video recording of dyskinesias.

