### Secondary outcomes:

Secondary outcome measures include the difference of UPRDS-III, IVa, and IVb from baseline after amantadine hydrochloride and after placebo administration. The changes of score from baseline will be compared between amantadine and placebo interventions.

UPDRS-III is scored on neurological examination performed by neurologists

UPDRS-IV is scored by interview.

Changes of UPDRS-IVa will be analyzed using a mixed linear model incorporating treatment effects (placebo vs active) and period effects (interaction of order effect and carry-over effect).

In addition secondary outcome measures include the correlation between blood concentrations of amantadine hydrochloride and the UPDRS (parts III and IV) and Rush Dyskinesia Scale changes.

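### The primary RDRS analysis reduces a graded change to improved/not-improved without a cut-off or a reason, which costs power and makes the test insensitive to worsening

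*Protocol*

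**What the plan says.** Section 12 (Primary outcome measure) takes as primary outcome the RDRS difference from baseline after each treatment, and adds: "The changes of scores from baseline will be compared between amantadine and placebo interventions". The method follows: "Changes of RDRS will be categorized into improved and not-improved, and data will be analyzed using repeated measure logistic regression", with treatment and period terms. No other model is named for RDRS. The section does not say what fall in score counts as improved, why the change is split, or which RDRS reading is the baseline.

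Two other parts of the protocol work on the graded scale:

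- Section 12 (Secondary outcomes): "Changes of UPDRS-IVa will be analyzed using a mixed linear model".
- Section 7 (Target sample size) compares two means, using the expectation that "dyskinesia score is expected to be improved by 1.1 (1.6) (mean (SD) points on the UPDRS-IVa by amantadine". The number of patients is "calculated as 30 (60 interventions) to achieve a power greater than 80% and an error of 0.05 in the crossover test".

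The design is a "multi-center, randomized, placebo-controlled, double-blind, cross-over study", so every patient is meant to supply an RDRS change on both treatments.

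**The concern.** The data will be graded and paired within patients, and the primary test uses little of either property.

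- **Size is lost.** A two-grade gain counts the same as a one-grade gain. A patient who gains two grades on amantadine and one on placebo is improved on both, and adds nothing to the within-patient contrast.
- **Direction is partly lost.** An unchanged patient and a worsened patient fall in the same class. The test is therefore insensitive to worsening dyskinesia.
- **Baseline error may enter the contrast.** If both treatments are judged against the same baseline reading, that reading cancels in a graded comparison but not after the split.
- **The analysis does not match the planning.** The trial is sized on means, and the secondary UPDRS-IVa change is modelled on its own scale. Only the primary outcome is dichotomised.

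At stake is whether 30 patients give the primary test the power that section 7 claims.

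**Working it through.** **Inputs from the protocol.** Mean 1.1 and SD 1.6 on UPDRS-IVa, 30 patients, power above 80% and an error of 0.05 (section 7); significance at 0.05 (section 12). No RDRS figure is given.

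**Assumptions.** Two-sided test; 15 patients per sequence; no period or carry-over effect; the UPDRS-IVa effect borrowed for RDRS; improved means a fall of at least 1 point. The protocol does not say whether 1.6 is the SD of the within-patient difference or of the change on each treatment, so both readings are run.

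**Step 1: the plan's own figure.** Normal approximation with z-values 1.960 and 0.842.

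- SD of the paired difference: n = ((1.960 + 0.842) × 1.6/1.1)² = 16.6, so 17 patients. With n = 30, power is 96% (95% by t).
- SD per treatment, two independent means: n = 2 × 16.6 = 33.2, so 34 per arm. With 30 per arm, power is 76% (74% by t).
- SD per treatment with within-patient correlation ρ: n = 33.2 × (1 − ρ). The stated 30 appears at ρ = 0.1 (29.9), a value the protocol does not give.

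So 30 patients exceed 80% power on the paired reading, for a graded analysis. This is not a calculation for a binary outcome.

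**Step 2: what happens to the baseline reading.** Let A, P and B be the scores on amantadine, on placebo and at a shared baseline. The graded contrast is (A − B) − (P − B) = A − P, and B drops out. After the split the contrast compares whether A − B and whether P − B pass the cut-off, so error in B stays in both. If the three readings vary independently with equal variance σ², the covariance of the two changes is σ² and each has variance 2σ², which gives a correlation of 0.5. Correlations of this order are therefore not extreme.

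**Step 3: power on the same simulated data.** Changes are drawn as correlated normals and rounded to whole points. The graded test is a period-adjusted cross-over t test. The binary test is logistic regression by generalised estimating equations (GEE) with treatment and period, 1,000 runs per scenario. Mean placebo change is 0 or −0.5 in the paired rows.

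| Reading of SD 1.6 | Correlation of the two changes | Graded | Binary | Loss (points) |
|---|---|---|---|---|
| Paired difference | 0 | 95% | 84% | 11 |
| Paired difference | 0.3 | about 94% | 77–80% | about 14–17 |
| Paired difference | 0.5 | 94% | 74% | about 20 |
| Paired difference | 0.7 | 94% | 63–67% | about 26–31 |
| Per treatment | 0 | 71% | 57% | 14 |
| Per treatment | 0.3 | 83% | 66% | 17 |
| Per treatment | 0.5 | 94% | 73% | 20 |

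With no treatment effect the GEE test rejected in 6 to 6.6% of runs, so its power is slightly flattered and the losses are slightly understated.

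**Step 4: a coarse scale.** The SD of each change is set to 0.3–0.5 point, so that most changes are 0 or 1. The effect is tuned to give the graded test about 80% or 95% power, and the binary test is a cross-over t test on improved status. The loss runs from about 0 (96.1% against 95.8%) to about 20 points (79.2% against 58.8%).

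**Step 5: a scale with a floor and a shared baseline.** On an assumed 0–4 scale with one baseline reading, and period-adjusted tests of about 4–6% size, the effect of 0.69 SD gave roughly 76–93% power graded against 52–69% binary.

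**The case against.** The strongest reply is that the protocol offers no RDRS data, so no single figure for the loss can be defended. The effect comes from an interview-scored scale, while RDRS is scored from video. The choice of binary test also matters: an asymptotic McNemar test loses up to about 43 points in the most extreme scenario, the planned type of model up to about 31. At zero correlation the logistic model still reached 84%. All of this stands. It limits the size of the claim but not its direction: dichotomising gained power in none of the scenarios run.

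Four stronger readings are tempting, and the protocol does not support them.

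- A reader might infer two rival primary tests at 0.05, one on scores and one on the split. The secondary-outcome paragraph has the same structure, a general sentence on comparing changes followed by the model. No second RDRS test is named.
- A reader might infer that the binary test cannot show harm. It can favour placebo if fewer patients improve on amantadine, and worsening may also show in the graded UPDRS-IVa analysis and in the adverse-event comparison. Insensitive is the right word.
- A reader might put a figure on patients who score zero at baseline and can never improve. Eligibility sets no minimum RDRS, but it requires patients "presenting dyskinesias of the limbs or the trunk". Any share rests on an invented distribution, and a floor also limits a graded score.
- A reader might take a single noisy baseline as given. Section 6 names the end of the observation period, but Table 1 also marks RDRS at Visit 1 and Visit 6, and no reliability figure is given. The argument in Step 2 of the working is conditional on a shared reading.

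**Conclusion.** The concern holds, as an inefficient and unexplained analysis choice that the protocol itself fixes. The primary outcome is declared as a graded change, and its only named model tests a two-class version with no stated cut-off.

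Under the borrowed UPDRS-IVa effect with 30 patients, the loss is roughly 10 to 30 points of power. It could be about 0 to 20 points if RDRS changes are nearly all 0 or 1 grade. These are illustrations that rest on the assumed correlations, placebo change and cut-off, and they are not bounds. In many scenarios the binary test falls below 80% while the graded test exceeds it. That is not so in all of them: at zero correlation both tests pass on the paired reading of the SD, and neither does on the per-treatment reading. It would go too far to say that the primary test is underpowered as a matter of fact.

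**What to change.** In section 12, name one graded within-patient RDRS analysis with treatment and period as the single decisive primary. One suitable choice is a period-adjusted rank test that compares the period-1-minus-period-2 RDRS differences between Arm 1 and Arm 2. It needs no assumption of normality.

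Keep a table of improved, unchanged and worsened by treatment, and the logistic model, as supportive analyses. State the cut-off for improved and which reading is the baseline.

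The cost is a change of wording, with no new data, visits or patients. The one downside is that the headline becomes a graded effect rather than a percentage improved, and that percentage is still reported.
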